### Interventions

#### Explanation for the choice of comparators {6b}

The PEx cohort is observational; therefore, no specific interventions are defined for this cohort. For the purpose of reporting a sub-study from the PEx cohort, a PERIT intervention is considered to be any treatment, procedure, or strategy used in the acute management of a PERIT. PERIT interventions in the sub-studies are grouped into therapeutic domains comprising sets of mutually exclusive interventions, for example, sets of backbone antibiotics, sets of adjunctive antibiotics, sets of mucolytic therapies, sets of alternative physiotherapeutic regimens, and sets of immunomodulator treatments.

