For each PERIT, we will also report the following outcomes measured as the following endpoints:The change in lung function up to 6 months after commencement of intensive therapy, *measured as* the absolute change in the ppFEV_1_ from initiation of intensive therapy until approximately 14 days (≥ 14 days to < 30 days), 30 days (≥ 30 days to < 60 days), 60 days (≥ 60 days to < 90 days), and 180 days (≥ 180 days to < 240 days) after commencement of intensive therapyThe change in lung function up to 6 months after commencement of intensive therapy, *measured as: (i)* the proportional change (expressed as a percentage) in the ppFEV_1_ from initiation of intensive therapy until 7 days (≥ 7 to < 10 days), 14 days (≥ 14 days to < 30 days), 30 days (≥ 30 days to < 60 days), 60 days (≥ 60 days to < 90 days), and 180 days (≥ 180 days to < 240 days) after commencement of intensive therapy; (ii) the return of measured lung function to close to its baseline (pre-exacerbation) best function, up to 6 months after commencement of intensive therapy, *measured as* a binary outcome of whether the ppFEV_1_ has returned to ≥ 90% of the ppFEV_1_ at baseline, at approximately 7 days (≥ 7 to < 10 days), 14 days (≥ 14 days to < 30 days), 30 days (≥ 30 days to < 60 days), 60 days (≥ 60 days to < 90 days), and 180 days (≥ 180 days to < 240 days) after commencement of intensive therapy, where the baseline ppFEV_1_ is the highest recorded ppFEV1 in the 180 days (or 365 days if no ppFEV_1_ < 180 days) preceding the commencement of intensive therapyThe change in CF-related symptoms up to 4 weeks after commencement of intensive therapy, *measured as* the absolute change in the Chronic Respiratory Infection Symptom Score (CRISS) score approximately 7 days (≥ 7 to < 10 days), 14 days (≥ 14 days to < 30 days), 30 days (≥ 30 days to < 60 days), after commencement of intensive therapyThe time to the next PERIT, *measured as* the time (in days) from commencement of intensive therapy to the next commencement of intensive therapy, after a period of no intensive therapy of ≥ 7 daysAdverse reactions resulting in treatment cessation, *measured as* any early termination of planned therapy before 7 days (7*24 hours) and before 14 days (14*24 hours) after commencement of intensive therapy, owing to one or more adverse events presumed by the responsible clinician to be attributable to the prescribed therapyTreatment failure resulting in treatment cessation, *measured as* any early termination of planned therapy before 7 days (7*24 hours) and before 14 days (14*24 hours) after commencement of intensive therapy, owing to inadequate improvement in symptoms or lung function, presumed by the responsible clinician to be attributable to a poor response to the prescribed therapy

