#### Participant timeline {13}

Once enrolled in the PEx Cohort, participants remain in the cohort until they withdraw, or until the project closes (see Criteria for Discontinuation above). The timing of individual PERITS varies between participants. Data collection occurs (1) at enrolment (cohort entry), (2) approximately every 3 months thereafter, and (3) with each PERIT (Fig. 3).

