	Date and details of any new, documented infection, or airway colonization	Y^a^	Y	The presence of specific pathogens may influence therapeutic choices, plausibly confounds or modifies treatment effects. Selection of resistant pathogens may be an untoward outcome of antibiotic therapy
	Date and details of any new, documented infection with *Clostridium difficile*	Y^a^	Y	*Clostridium difficile*-related diarrhea is an important untoward outcome of antibiotic therapy
**Patient-reported outcomes**:	Cystic Fibrosis Questionnaire-revised (CFQ-R) for all participants ≥6 years old	Y	Y	Treatment of PEx plausibly impacts on quality-of-life (QoL) over time
**Anthropometric**	Height	Y	Y	Height is associated with FEV_1_ and is essential for estimating the ppFEV_1_
	Weight	Y	Y	Treatment of PEx plausibly impacts on weight over time
**Spirometry**	FEV_1_	Y^b^	Y	Treatment of PEx plausibly impacts on lung function. The ppFEV_1_, is strongly associated with morbidity and mortality in CF

^a^Including results in the 24 months preceding enrolment into the cohort

^b^Including results in the 12 months (365 days) preceding enrolment into the cohort

**Table 2 Tab2:** Additional outcome data for each PERIT

	Variable	Timing	Reason
**PEx therapy**	Date and time of commencing IV therapy	Day 0	As a time reference point for analyses
**PEx therapy**	Location (hospital or HITH)	Daily	For description of the cohort. Location may constrain therapeutic options and plausibly confound or modify treatment effects
**Spirometry**	FEV_1_	Days 0 (at admission), 7, 14, 30, 60, and 180	Treatment of PEx plausibly impacts on lung function, measured as ppFEV_1_; this is strongly associated with morbidity and mortality in CF
**Clinical assessment**	Presence and quality of cough	Daily	Reduction in cough and/or improvement in cough quality are measures of successful treatment of PEx
	Presence of crepitations	Daily	Reduction in crepitations is a measure of successful treatment of PEx
**Patient-reported outcomes**	CRISS score (if > 12 years at admission)	Day 0: as close as practicable to the initiation of IV antibiotics, and not > 72 h afterwards, then days 7, 14, and 30	CRISS is a validated measure of CF-related symptoms in the preceding 24 h. It is expected that successful treatment will result in an improved CRISS score. It will be used to assess clinical response to treatment for PEx

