## Discussion

The BEAT CF PEx core protocol sets out a prospective cohort designed to perpetually enroll people with CF to evaluate the comparative effectiveness of interventions used for managing PEx. It is intended that sub-studies will be nested within this cohort in order to generate high-quality evidence to optimize the management of PEx.

The primary endpoint is the absolute change in ppFEV_1_ approximately 7 days after initiation of intensive therapy. FEV1 is a practical and objective endpoint for PEx which has been shown to correlate with quality of life, mortality and with structural lung changes, making it the most widely used clinical trial endpoint in CF [13]. Increasingly spirometry can be performed in the home using calibrated personal spirometry devices, meaning it may not be necessary for assessments to be performed in hospital. We have selected a short-term primary endpoint to inform guidance on treatment decisions in the first week of intensive therapy, even though other trials have typically assessed responses to treatment after several weeks. CF physicians often change therapy if there is unsatisfactory clinical response after 7–10 days [14], so measuring the primary outcome at a later time point will introduce an unacceptable amount of treatment crossover that will complicate interpretation of the results. Published data indicate that most of the improvement in FEV_1_ following treatment for exacerbations occurs within the first week of intensive therapy [15], and the short-term change in FEV_1_ is strongly predictive of the longer term change in FEV_1_ [16]. From a practical perspective, most CF centers re-check the FEV_1_ after 7–10 days or have opportunity to do so, and a recent trial found evidence that it is acceptable to curtail antibiotic treatment to just 10 days of intravenous therapy in those with an acceptable FEV_1_ and symptom response after 7 days of therapy [17]. In summary, measurement of ppFEV_1_ as the primary endpoint at a timepoint where CF physicians typically measure FEV_1_ and make decisions about future treatment allows a robust outcome measure that will be clinically informative.

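### The return-to-baseline endpoint uses the highest of an uncontrolled number of prior readings, so with equal true recovery, participants measured more often are scored as returned less often

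*Protocol article*

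**What the plan says.** Outcomes {12} of the protocol article defines a binary secondary endpoint at each follow-up window from day 7 to day 180: "whether the ppFEV_1_ has returned to ≥ 90% of the ppFEV_1_ at baseline". Baseline is the "highest recorded ppFEV1 in the 180 days" before intensive therapy starts, with a 365-day window if the 180-day window is empty. The outcome is described as a return close to the participant's best pre-exacerbation function. No minimum, maximum or standard number of readings is set.

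Three places determine how many readings a participant will have:

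- Participant timeline {13} collects data at entry, then "approximately every 3 months thereafter", and with each PERIT.
- Table 2 under {18a} schedules FEV1 for every PERIT at "Days 0 (at admission), 7, 14, 30, 60, and 180", which is one reading per follow-up time point.
- Table 1, footnote b, adds for new enrollees whatever spirometry was recorded in the year before enrolment: "Including results in the 12 months (365 days) preceding enrolment into the cohort".

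The section on choice of comparators {6b} states: "The PEx cohort is observational; therefore, no specific interventions are defined for this cohort".

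**The concern.** One side of the comparison is, by schedule, a single noisy reading. The other is the largest of several noisy readings. The expected maximum grows with the number of readings even when true lung function is constant, so the 90% threshold moves up with measurement frequency. A participant who had a PERIT a few months ago faces a higher bar than an equally recovered participant seen only at quarterly visits.

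The endpoint then partly records how often someone was tested. The cohort exists to compare interventions, and outside the randomised sub-studies nothing in the design balances reading frequency between treatments. If frequency differs between treatment groups, the contrast is biased. Adjusting for disease severity alone need not remove this, because the error comes from the count of readings. Outcomes {12} states adjustment for baseline factors only for the primary effect measure.

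**Working it through.** **No figure to reproduce.** The protocol gives no expected return rate, sample size or power for this endpoint.

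**Number of readings in 180 days, from the schedule.** Quarterly collection gives 180/90 = 2. One earlier PERIT inside the window adds days 0, 7, 14, 30 and 60, which is 5, so up to 2 + 5 = 7. Its day 180 reading falls at or beyond the window length and is not counted.

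**Model.** The participant is fully back to a true level μ. The follow-up reading is F ~ N(μ, σ). Prior readings are B_i ~ N(μ + δ_i, σ), independent, where δ_i is how far the participant was below the usual level at that reading. The participant is scored as returned if F ≥ 0.9 × max(B_i). Conditioning on F,

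P(returned) = ∫ φ(x) ∏_i Φ( [ (μ + σx)/0.9 − μ − δ_i ] / σ ) dx.

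σ is an assumption, shown from 2 to 5 points; μ is set at 60 and 80.

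**All prior readings at the usual level (δ_i = 0), P(returned) in %:**

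| μ | σ | n=1 | n=2 | n=4 | n=7 | loss from 2 to 4 |
|---|---|---|---|---|---|---|
| 60 | 2 | 98.7 | 97.6 | 95.9 | 93.9 | 1.7 |
| 60 | 3 | 93.1 | 88.4 | 81.9 | 75.4 | 6.6 |
| 60 | 4 | 86.8 | 78.8 | 68.8 | 60.0 | 10.0 |
| 60 | 5 | 81.4 | 71.2 | 59.4 | 49.7 | 11.8 |
| 80 | 2 | 99.9 | 99.7 | 99.5 | 99.2 | 0.2 |
| 80 | 3 | 97.6 | 95.8 | 92.8 | 89.6 | 2.9 |
| 80 | 4 | 93.1 | 88.4 | 81.9 | 75.4 | 6.6 |
| 80 | 5 | 88.3 | 81.0 | 71.7 | 63.3 | 9.3 |

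(Losses are computed before rounding.) The n=7 column is an upper bound, because readings early in an earlier PERIT are usually depressed.

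**Two routine readings plus five depressed readings from one earlier PERIT.** The offsets at days 0, 7, 14, 30 and 60 are assumptions.

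- *Quick recovery* (−8, −3, −1, 0, 0). At μ = 60 and σ = 4, P(returned) falls from 78.8% to 65.8%, close to the result for 4 to 5 readings at the usual level. The loss over both μ is 3.6 to 15.9 points at σ = 3 to 5, and 2.0 or less at σ = 2.
- *Clearly depressed throughout* (−10, −6, −4, −3, −2). The loss is 1.9, 4.9 and 7.8 points at μ = 60 and 0.7, 2.9 and 5.8 at μ = 80, for σ = 3, 4 and 5. At σ = 2 it is 0.1 or less.

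**Sensitivity to the model, loss from 2 to 4 readings,** with σ as 5%, 8% and 10% of the true level:

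- Prior readings correlated at 0.5: 89.7 − 85.6 = 4.1, 75.4 − 68.2 = 7.2 and 68.9 − 60.7 = 8.2 points.
- Either of two follow-up readings counts: 96.8 − 94.3 = 2.5, 88.1 − 80.4 = 7.7 and 82.9 − 73.1 = 9.8 points.

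Both soften the effect; neither removes it.

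**The case against.** **The maximum is intended.** The outcome is return to near best function, and the 90% allowance sits below that best value. On this view a participant with few readings simply has the best value under-captured. This stands as a reason to keep the definition. It does not make a maximum of 2 and a maximum of 7 the same quantity.

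**The size rests on assumptions.** This stands. The documents give no within-person SD, and Background {6a} itself says about a quarter of people do not fully regain lung function, so readings after an earlier PERIT may stay low. With small noise or clear depression the effect is a few points or less.

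**The analysis plan may deal with it.** Covariates for a secondary model often sit there, and it is not shown. But the reference rule is fixed in the protocol, and it places no limit on the number of readings.

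**Several follow-up readings may fall in one window.** Outcomes {12} does not say which would count. The single reading comes from the Table 2 schedule, and a second one reduces the effect only in part.

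Stronger readings are tempting but not supported:

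- *Dozens of home readings feeding the maximum.* The Discussion says "Increasingly spirometry can be performed in the home using calibrated personal spirometry devices", but the point made there is where assessments take place. Tables 1 and 2 contain no home series.
- *A demonstrated bias between treatments.* No passage shows that frequently measured participants receive different interventions. It is plausible in routine care, but if frequency is unrelated to treatment the harm is misclassification and lost sensitivity.
- *A threat to the main result.* The primary endpoint and the absolute and proportional change endpoints start from the reading at initiation of therapy and do not use this maximum.

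**Conclusion.** The concern holds for this one secondary endpoint. The direction needs only some within-person variation: extra readings cannot lower the maximum, so they cannot raise the chance of being scored as returned. Unequal counts follow from the protocol's own schedule.

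The size is conditional. Going from 2 to 4 effective readings costs about 3 to 12 percentage points at an assumed SD of 3 to 5, and 2 or less at SD 2. When the readings of an earlier PERIT stay clearly depressed, adding all five costs about 1 to 8 points at SD 3 to 5. These figures assume full recovery, normal independent readings and one follow-up reading.

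The bias risk applies to the observational comparisons. In randomised sub-studies reading counts should balance, leaving some loss of sensitivity.

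**What to change.** Keep the reference as the highest reading, since best function is the declared target, and add two things:

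1. Prespecify the number of ppFEV1 readings in the reference window as a covariate in every comparative model of this endpoint. Let its effect be non-linear, because each further reading matters less than the last.
2. Report a sensitivity analysis with a reference standardised for reading count, for example a single specified pre-exacerbation routine reading, with pre-enrolment results allowed for new enrollees.

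Restricting the maximum to routine quarterly visits would not be enough. Attendance can still leave 0 to 3 readings, and 1 against 2 readings alone is a gap of 86.8 − 78.8 = 8.0 points at ppFEV1 60 and SD 4. New enrollees might also have no quarterly reading.

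The cost is one covariate and one derived variable, with no new data collection. The standardised reference ignores some true best values, which is why it belongs in a sensitivity analysis.

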#### Participant timeline {13}

Once enrolled in the PEx Cohort, participants remain in the cohort until they withdraw, or until the project closes (see Criteria for Discontinuation above). The timing of individual PERITS varies between participants. Data collection occurs (1) at enrolment (cohort entry), (2) approximately every 3 months thereafter, and (3) with each PERIT (Fig. 3).

**Fig. 3 Fig3:**
[figure not shown]
Enrolment and data collection timeline for PEx cohort participants

#### Sample size {14}

There is no maximum sample size for the PEx Cohort, although target or maximum sample sizes may apply to cohort-nested sub-studies, and these will be specified in their relevant subprotocols.

#### Recruitment {15}

A broad patient enrolment approach is taken with the aim of enrolling all willing and eligible people with CF. Potential screening avenues to identify eligible patients include:During clinic appointments —potential participants may be directly approached during routine clinic appointments conducted by participating sites. Trained research staff will, after consulting with the clinical team, approach patients (or their parents) to discuss participation in the PEx cohortAdvertising material approved by the relevant Human Research Ethics Committee (HREC), including posters, brochures, and social media, may be used to promote and raise awareness of the project; these will appear in participating hospitals on notice boards or electronic notice boards. Advertisements may also be displayed in various community locations to assist enrolmentLetters—a HREC approved letter for distribution by participating sites to potential participants is supplied to all participating sitesBEAT CF website—a publicly accessible website where participants and their families can access the Participant Information Booklet, read updates about BEAT CF, and learn about the rationale and the team undertaking the research. This includes a section where interested people can receive further information or register their interest with contact details if they want to participateSocial media—the approved advertisements and other example promotional content is distributed through various social media avenues of the sponsor and supporting organizations, including Cystic Fibrosis Australia and its state branches

Research staff at participating sites are trained on project requirements prior to screening and enrolment of participants to ensure eligible participants are identified, educated about, and invited to participate in the PEx cohort. Enrolment and screening procedures occur according to the approved protocol and in line with the principles of Good Clinical Practice (GCP). Documented instructions for operational matters are provided to participating sites detailing enrolment, screening, and data collection procedures. Reasons for non-eligibility are recorded in a screening log.

### Assignment of interventions: allocation

#### Sequence generation {16a}

The PEx cohort does not entail any assignment of interventions, except as may be required by participation in any nested sub-studies. Methods for generating allocation sequences for those studies will be specified within the relevant subprotocols or their appendices.

#### Concealment mechanism {16b}

The PEx cohort does not entail any assignment of interventions, except as may be required by participation in any nested substudies. Methods for concealing the treatment assignment for those studies will be specified within the relevant subprotocols or their appendices.

#### Implementation {16c}

The PEx cohort does not entail any assignment of interventions, except as may be required by participation in any nested substudies. Methods for implementing the treatment assignment for those studies will be specified within the relevant subprotocols or their appendices.

### Assignment of interventions: blinding

#### Who will be blinded {17a}

The PEx cohort does not entail assignment of any interventions, except as may be required by participation in any nested sub-studies. Methods for implementing any blinding for those studies will be specified within the relevant sub-protocols or their appendices.

#### Procedure for unblinding if needed {17b}

Unblinding is not relevant for the PEx cohort. Where relevant, any procedures for unblinding for any nested sub-studies will be specified within the relevant subprotocols or their appendices.

### Data collection and management

#### Plans for assessment and collection of outcomes {18a}

PEx cohort data is collected on electronic and/or hard copy case report forms (eCRF/CRF) pertaining to (i) clinical and demographic data, (ii) disease characteristics (including pancreatic exocrine status, CF-related diabetes, genotype), (iii) anthropometric data (including height and weight), (iv) lung function, (v) PERITs including the treatment(s) received, serial lung function measurements at defined time points and laboratory and clinical outcomes, (vi) microbiological outcomes, and (vii) patient-reported outcomes. Tables 1 and 2 provide justifications for the collection of data in the PEx cohort, specific for individuals and PERITs, respectively. However, sub-studies may require the additional collection of these variables at different time points, which will be specified within the relevant subprotocols and appendices.

**Table 1 Tab1:** Outcome data for BEAT-CF participants

Category	Variable	Timing		Justification
		At cohort entry	3-monthly	
**Demographic data**	Date of birth	Y		Age is independently associated with baseline lung function in CF. There may be “cohort” effects whereby those born in more recent periods have better outcomes because of improvements in care
	Sex	Y		Sex is independently associated with lung function in CF
**Clinical**	Genotype	Y		Validation of CF diagnosis
	Sweat test results	Y		Validation of CF diagnosis
	Pancreatic exocrine status	Y	Y	Pancreatic function is independently associated with lung function in CF
	CF-related diabetes	Y	Y	Diabetes is independently associated with lung function in CF
	Known drug allergies or contraindications	Y	Y	Drug allergies and contraindications constrain therapeutic options, and plausibly confounds or modifies treatment effects
	Concomitant medications	Y	Y	Use of concomitant medications plausibly confounds or modifies treatment effects, including toxicities
**Laboratory**	Total IgE	Y^a^	Y	Marker for allergic bronchopulmonary aspergillosis which is a cause of clinical deterioration and may confound PEx management
	*Aspergillus*-specific RAST	Y^a^	Y	Marker for allergic bronchopulmonary aspergillosis which is a cause of clinical deterioration and may confound PEx management
	Date and details of any new, documented infection, or airway colonization	Y^a^	Y	The presence of specific pathogens may influence therapeutic choices, plausibly confounds or modifies treatment effects. Selection of resistant pathogens may be an untoward outcome of antibiotic therapy
	Date and details of any new, documented infection with *Clostridium difficile*	Y^a^	Y	*Clostridium difficile*-related diarrhea is an important untoward outcome of antibiotic therapy
**Patient-reported outcomes**:	Cystic Fibrosis Questionnaire-revised (CFQ-R) for all participants ≥6 years old	Y	Y	Treatment of PEx plausibly impacts on quality-of-life (QoL) over time
**Anthropometric**	Height	Y	Y	Height is associated with FEV_1_ and is essential for estimating the ppFEV_1_
	Weight	Y	Y	Treatment of PEx plausibly impacts on weight over time
**Spirometry**	FEV_1_	Y^b^	Y	Treatment of PEx plausibly impacts on lung function. The ppFEV_1_, is strongly associated with morbidity and mortality in CF

^a^Including results in the 24 months preceding enrolment into the cohort

^b^Including results in the 12 months (365 days) preceding enrolment into the cohort

**Table 2 Tab2:** Additional outcome data for each PERIT

	Variable	Timing	Reason
**PEx therapy**	Date and time of commencing IV therapy	Day 0	As a time reference point for analyses
**PEx therapy**	Location (hospital or HITH)	Daily	For description of the cohort. Location may constrain therapeutic options and plausibly confound or modify treatment effects
**Spirometry**	FEV_1_	Days 0 (at admission), 7, 14, 30, 60, and 180	Treatment of PEx plausibly impacts on lung function, measured as ppFEV_1_; this is strongly associated with morbidity and mortality in CF
**Clinical assessment**	Presence and quality of cough	Daily	Reduction in cough and/or improvement in cough quality are measures of successful treatment of PEx
	Presence of crepitations	Daily	Reduction in crepitations is a measure of successful treatment of PEx
**Patient-reported outcomes**	CRISS score (if > 12 years at admission)	Day 0: as close as practicable to the initiation of IV antibiotics, and not > 72 h afterwards, then days 7, 14, and 30	CRISS is a validated measure of CF-related symptoms in the preceding 24 h. It is expected that successful treatment will result in an improved CRISS score. It will be used to assess clinical response to treatment for PEx

Electronic patient-reported outcome (ePRO) tools are used to collect symptom and quality of life (QoL) data. These tools include:Cystic Fibrosis Respiratory Symptoms Diary-Chronic Respiratory Infection Symptom Score (CFRSD-CRISS): a validated instrument in adults and children ≥ 12 years old which captures symptoms in the preceding 24 h [11]CFQ-R: available in four versions (adults, adolescents, young children, and parents) in 34 languages and is a validated quality of life (QoL) instrument for use in adults and children > 6 years. This tool quantifies the impact of disease and treatment on overall health status and perceived well-being and includes an assessment of symptoms, treatment burden, and the integrity of relationships within the preceding 2 weeks [12]

